### Study population

The study population will consist of adults with anxiety disorders with the following criteria for inclusion: age 18 years or older with panic disorder, specific phobia, agoraphobia, or social phobia according to the DSM-IV [25] as assessed with the Mini International Neuropsychiatric Interview (MINI) [26], and having given signed informed consent. Criteria for exclusion will be suicidal risk, an ongoing episode of bipolar disorder or psychosis, concurrent psychological treatment for the anxiety disorder, considered unable to attend the intervention as planned (due to vacation, work/study placement, sickness, or similar occurrences), or lack of informed consent.

### Sample size

The primary feasibility outcome is the number of randomised participants divided by the number of all eligible people for the trial. Eligible people are those who fulfil the inclusion criteria of our trial. If the number of randomised participants is 64 out of 100 eligible people then the proportion will be 64 % with 95 % confidence interval (CI) between 50 and 78 %. A proportion of 50 % or more randomised participants will be acceptable for a future trial. In contrast, if the likely sample proportion is less than 50 %, we will have difficulties with recruiting participants for a large trial as well as with generalisability of results.

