## Methods/design

### Trial design

The trial is an investigator-initiated, feasibility randomised controlled trial investigating ICBT with FearFighter™ compared with no intervention for adults with an anxiety disorder. We have followed the Standardised Protocol Interventions: Recommendations for Interventional Trials (SPIRIT) 2013 Statement which defines standard protocol items for clinical trials [20]. The Copenhagen Trial Unit (CTU) is responsible for the centralised randomisation. The randomisation is carried out according to a web-based computer-generated allocation sequence with varying block sizes kept unknown to the investigators. Once a participant is assessed as eligible for the trial the trial secretary will use the web-based randomisation system to allocate the participant to an intervention group. The allocation ratio is 1:1. Based on evidence of prognostic factors, the randomisation is stratified into: (1) social phobia and panic with agoraphobia, and (2) panic disorder without agoraphobia and specific phobia [21, 22]. Participants with panic disorder without agoraphobia and specific phobia have a distinctively higher remission rates than other types of anxiety [21, 22]. Assessment will be conducted prior to randomisation and start of intervention (week 0), at post-intervention (week 10), and at follow-up (week 37) (see the flow chart in Figure 1 in the Appendix). The trial has been approved by the Regional Ethical Committee for the Capital Region of Denmark (journal number: H-15005836), and by the Danish Data Protection Agency (journal number; RHP-2015-009 I-Suite 03652). The trial is registered at ClinicalTrials.gov at the United States National Institutes of Health (Identifier: NCT02499055, registered on 1 July 2015).

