### Recruitment and procedure

Participants are recruited via advertisements through the Danish Student Counselling Service and their website (www.srg.dk) with a link to our trial website. Our trial website contains information about the trial and a Contact Form for prospective trial participants. People visiting our trial website are asked to answer three screening questions from the Improving Access to Psychological Therapies (IAPT) Phobia Scale about how much they would avoid three different anxiety-provoking situations [27]. People who screen positive for a minimum of one of the three anxiety symptoms on the IAPT Phobia Scale are invited to sign up for an initial interview. A psychologist (the support person for FearFighter™) conducts the initial interview face-to-face (see Table 1 for an overview). Danish Regional Ethical Committee-approved written information about the trial is presented to interested people alongside with information about alternative places to receive advice and treatment for their anxiety. The interested people are advised not to participate in the trial if they need help urgently or if they consider the duration of the trial to be too long. The people are subsequently assessed with the use of the MINI and the Standardised Assessment of Personality Abbreviated Scale (SAPAS). The MINI is a diagnostic instrument for major axis I psychiatric disorders and is used to identify people with an anxiety disorder and the presence of comorbidity. As the MINI does not identify or screen for personality disorders, the SAPAS is used as a screening instrument [28]. The SAPAS will only be used for background information to indicate the possible presence of comorbid personality disorders in a person. People will be eligible as participants if they comply with the inclusion and exclusion criteria. If a person gives their written informed consent to become a participant in the trial they will be randomised. All people are informed that they may withdraw their consent at any time during the trial.

**Table 1 Tab1:** Assessment tests and times of data collection in the FearFighter™ feasibility trial

Name of test	Screening/ website	Initial trial interview (week 0)	During trial	End-of-trial interview (week 10)	Follow-up (week 37)
Phobia Scale^a^	Xe		Xe		
Sociodemographic data		Xp			
Mini International Neuropsychiatric Interview		Xp		Xp	Xp
Standardised Assessment of Personality Abbreviated Scale		Xp			
Beck Anxiety Inventory		Xe		Xe	Xe

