## Outcomes

### Feasibility outcomes

The primary feasibility outcome is the proportion of randomised participants out of all eligible people. Eligible participants are those who fulfil our inclusion criteria. The secondary feasibility outcome is compliance, defined as the number of participants completing at least six of the nine planned FearFighter™ sessions in the experimental group. FearFighter™ will automatically register time for login and save the exercises that have been completed. The support person sees a tracking log on the administration webpage for FearFighter™ for each participant and the compliance will be assessed during the weekly telephone calls with the experimental participants and summed-up at the end of the trial interview.

Participants who complete six or more sessions in FearFighter™ but who fail to show up for post-treatment assessment are still regarded as completers in the feasibility outcome. If the participants complete less than six sessions they will be regarded as noncompleters (dropouts).

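### The denominator of the primary feasibility outcome is defined inconsistently, and on a literal reading it leaves out everyone who declines consent

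*Protocol article*

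**What the plan says.** **The outcome and its denominator.** Sample size states: "The primary feasibility outcome is the number of randomised participants divided by the number of all eligible people for the trial". It continues: "Eligible people are those who fulfil the inclusion criteria of our trial". Feasibility outcomes repeats this: "Eligible participants are those who fulfil our inclusion criteria".

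**The criteria.** Study population closes its inclusion list with "and having given signed informed consent" and its exclusion list with "or lack of informed consent", so consent stands in both. The Abstract (Methods and design) gives a single inclusion criterion, an anxiety disorder on the MINI, and places consent only among the exclusions.

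**The procedure.** Recruitment and procedure uses a wider rule: "People will be eligible as participants if they comply with the inclusion and exclusion criteria". The next step is: "If a person gives their written informed consent to become a participant in the trial they will be randomised". Trial design puts no step between eligibility and allocation: "Once a participant is assessed as eligible for the trial the trial secretary will use the web-based randomisation system to allocate the participant".

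**How the outcome is used.** The Abstract asks for a lower 95 % confidence limit of at least 50 %. Sample size plans on 64 randomised out of 100 eligible. Statistical analyses derives the 50 % threshold from pretreatment attrition in earlier studies. Table 2 takes N as the count of eligible people who have to be examined before 64 are randomised.

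**The concern.** The outcome is meant to show whether enough suitable people will enter a trial of this kind. The main way a suitable person fails to enter is by declining. If consent is part of eligibility, a decliner drops out of the denominator along with the numerator, and refusal no longer affects the result.

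Separately, the sections disagree on whether people with a clinical exclusion count. Sample size and Feasibility outcomes apply the inclusion criteria alone; Recruitment and procedure applies both lists.

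This is the primary outcome and, according to the Discussion, one of the two conditions for going on to a large trial. The Background reports that the previous Danish trial of the programme recruited poorly, so uptake is the question that this trial most needs to answer.

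**Working it through.** **Inputs.** From the article: 64 randomised; success if the lower 95 % limit is at least 50 % (Abstract); planning case 64/100 (Sample size). Assumed for illustration only: 110 people assessed who meet the age and diagnosis criteria, of whom 10 have a clinical exclusion and 36 of the rest decline, leaving 110 − 10 − 36 = 64.

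**Step 1: the article's own figure.** For 64/100 the article gives 50 to 78 %. The Wald interval is 0.64 ± 1.96 × √(0.64 × 0.36/100) = 0.64 ± 0.094, or 54.6 to 73.4 %. Wilson gives 54.2 to 72.7 % and the exact (Clopper-Pearson) method 53.8 to 73.4 %. The stated interval is not reproduced. That is a separate matter and the present point does not depend on it.

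**Step 2: the formula.** The exact lower limit L for 64 out of N solves P(X ≥ 64 | N, L) = 0.025, so L is the 2.5 % quantile of a Beta(64, N − 63) distribution. For N = 64 this reduces to L = 0.025^(1/64) = 0.944.

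**Step 3: the same assumed people under each reading.**

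| Reading of 'eligible' | Fraction | Proportion | Exact lower limit | Criterion |
|---|---|---|---|---|
| Both lists, consent in each (Recruitment and procedure with Study population) | 64/64 | 100 % | 94.4 % | met |
| Inclusion list only, consent in it (Sample size with Study population), if all 10 excluded people had signed | 64/74 | 86.5 % | 76.5 % | met |
| Clinical eligibility before consent | 64/100 | 64.0 % | 53.8 % | met |
| Inclusion criterion only, without consent (Sample size with the Abstract) | 64/110 | 58.2 % | 48.4 % | not met |

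If none of the 10 had signed, the second row becomes 64/64.

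**Step 4: where the criterion turns.** At N = 106 the exact lower limit is 50.4 %; at N = 107 it is 49.9 %. By Wald or Wilson the last passing N is 107.

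**Step 5: sensitivity to refusal.** With decliners in the denominator and N = 64 / consent rate (rounded):

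- consent 50 %: 64/128, lower limit 41.0 %, not met
- consent 60 %: 64/107, lower limit 49.9 %, narrowly not met
- consent 80 %: 64/80, lower limit 69.6 %, met

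Under the first reading in the table, all three cases are reported as 64/64.

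**Step 6: the planning case.** 100 − 64 = 36 people who are eligible but not randomised. If both lists apply and all who consent are randomised, there can be no such people. If only the inclusion list applies, with consent in it, the 36 would have to be people who consented and were then excluded.

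**The case against.** The strongest reply is that a count before consent was plainly intended. The Abstract's inclusion criterion does not mention consent. Recruitment and procedure describes information, then the MINI, then eligibility, and only then a conditional sentence about consent, which implies that some eligible people will not give it. Table 2 makes sense only if eligible people can go unrandomised, and so does the 64/100 example. The article also condenses a fuller protocol, and its flow chart is not shown.

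Much of this stands. A reader might infer that the outcome is 100 % by construction and cannot fail. The documents do not support that. It holds strictly only when both lists of Study population are applied as in Recruitment and procedure. Under the inclusion-only wording, people who consent and are then excluded stay in the denominator, so the value can fall below 100 %; failing by that route would need about 40 % of consenters to be excluded (43/107), which is unlikely because consent follows assessment. Read with the Abstract, the same wording keeps decliners in, and the outcome can fail outright. Nor does the text show how the count will actually be made.

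What does not stand is that intent settles the matter. The definition is not missing; it is stated twice, by reference to criteria that include consent in Study population. And even if a pre-consent count is granted, the sections still disagree on people with a clinical exclusion, which is the difference between 64/100 and 64/110 in the example.

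**Conclusion.** The point holds as an inconsistent definition of the primary outcome, one literal reading of which gives a wrong answer. On that reading the result is at or near 100 %, with a lower limit of about 94 %, whatever the refusal rate. On the other available readings the assumed example gives lower limits from 76.5 % down to 48.4 %, so the definition alone can turn a pass into a fail.

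The conflict between the sections rests on the text alone. The spread of results rests on the assumed 110, 10 and 36. The turning point at 106/107 rests on the exact method and on the lower-limit criterion. Sample size and the Discussion also word the threshold as a plain proportion; on that rule the turning point would be 128 eligible people (64/128 = 50 %), and the choice of denominator would still matter.

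**What to change.** Use one definition in Sample size, Recruitment and procedure, Feasibility outcomes and Statistical analyses (including Table 2). For this outcome, eligible means everyone assessed at the initial interview who is 18 or older, has a qualifying MINI diagnosis and has no exclusion criterion other than lack of consent. Add three statements:

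- Consent is not part of eligibility for this outcome, and people who decline stay in the denominator.
- People with a clinical exclusion are not counted. This departs from the inclusion-only wording of Sample size and Feasibility outcomes, so it should be stated openly as a choice: in the example it moves the result from 64/110 to 64/100.
- The number who decline before the MINI is reported separately. Written information, and advice on who should not take part, come before the MINI, so these people have no diagnosis and this denominator cannot capture them.

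The cost is a change of wording plus one extra count at the interview. The downside is that the reported proportion will be lower than under the literal wording.

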**Methods and design:**

We will conduct an investigator-initiated, feasibility randomised controlled trial. Sixty-four participants are expected to be recruited via an advertisement posted on the homepage of the Student Counselling Service in Denmark. The inclusion criterion for participation in the trial will be the presence of anxiety disorder as assessed with the Mini International Neuropsychiatric Interview. The exclusion criteria will be suicidal risk, an ongoing episode of bipolar disorder or psychosis, concurrent psychological treatment for the anxiety disorder, considered unable to attend the intervention as planned (due to vacation, work/study placement, sickness, or similar occurrences), or lack of informed consent. The intervention group will be offered nine sessions with the ICBT programme FearFighter™ and a weekly telephone contact to support compliance. The control group will receive no intervention. We define the feasibility outcomes as follows: the fraction of randomised participants out of the eligible people (the lower 95 % confidence interval (CI) ≥ 50 %); and the fraction of compliant participants (those receiving at least six out of nine sessions) in the intervention group (the lower 95 % CI ≥ 60 %). The exploratory clinical outcomes are the number of participants no longer meeting the diagnostic criteria for an anxiety disorder at the end of the trial and level of distress (Beck Anxiety Inventory, Symptom Checklist-90-R, WHO Well-Being Index, Sheehan Disability Scale); the number of severe adverse events; and the occurrence of any psychological treatment outside the trial.

To prevent bias in design, and in the gathering and analysis of data throughout the trial, we will follow the SPIRIT 2013 statement which defines standard protocol items for clinical trials.

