### Statistical analyses

The primary feasibility outcome is defined as the number of participants randomised out of the people considered eligible for being randomised in the trial. Based on observations regarding pretreatment attrition in CBT and IBT for anxiety disorders studies [9, 36–38], we will consider the feasibility outcome satisfactory if it is over 50 %. Our hypothesis is that we are sampling from a population of eligible people of whom at least half will be randomised. If we let *N* be the observed number of eligible people needed to randomise a sample of 64 participants, then in a random sample of size *n* sampled from a population sized *N*, *n/N* follows a binomial distribution with a lower 95 % CI of over 50 % [39, 40]. The sample size estimated from the primary feasibility outcome implicitly defines the sample sizes to be used in the assessment of the exploratory clinical outcomes (Table 1).

The secondary feasibility outcome for the participants in the experimental group is defined as the number of participants completing at least six out of nine FearFighter™ sessions. This feasibility outcome is considered satisfactory when the lower 95 % CI is over 60 % based on observations for completer fractions in IBT for anxiety disorders [9, 41]. In a random sample of size *n* of completers sampled from a population sized *N* of participants in the experimental group, *n*/*N* follows a binomial distribution with a lower 95 % CI over 60 %.

The exploratory clinical outcomes will be analysed using the general linear model (GLM) logistic regression, or the proportional odds model for ordinal outcomes as appropriate, adjusting for the stratification variables and baseline scores of the outcomes according to Table 2. We will calculate two-sided tests and use the resulting *p* values as a data-reducing device because test results with *p* values < 0.05 will be used to select hypothesis-generating outcomes.

**Table 2 Tab2:** Feasibility outcomes and exploratory clinical outcomes in the Fearfighter™ feasibility trial

	Rating scales	Type of outcome	Test
Feasibility outcome			
Number of randomised participants/eligible persons	Not relevant	Proportion	Calculate the probability that 64/*N* can have been obtained in a random sample of *N* participants obtained from a population of persons where half the eligible persons can be randomised. (*N* is the observed number of eligible persons necessary to examine to randomise 64 participants)

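### The 95 % interval given for 64 randomised of 100 eligible is wrong (about 54 to 73 %, not 50 to 78 %), so the only precision figure behind the sample size needs restating; the error is conservative and leaves 64 and the decision rule unchanged

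*Protocol article*

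**What the plan says.** The Sample size section of the protocol article contains one calculation. It opens "If the number of randomised participants is 64 out of 100 eligible people" and gives the result as "64 % with 95 % confidence interval (CI) between 50 and 78" per cent. It then says that a proportion of at least 50 % would be acceptable for a future trial. There is no power, effect size or other precision figure in that section.

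The success criterion for this outcome appears in two other places. The Abstract (Methods and design) requires "the lower 95 % confidence interval (CI) ≥ 50" per cent. The Statistical analyses section says that the proportion "follows a binomial distribution with a lower 95 % CI of over 50" per cent. Table 2 makes clear that 64 is fixed and that the denominator *N* "is the observed number of eligible persons necessary to examine to randomise 64 participants".

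The Statistical analyses section also ties the trial's size to this outcome: "The sample size estimated from the primary feasibility outcome implicitly defines the sample sizes to be used in the assessment of the exploratory clinical outcomes".

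**The concern.** The inputs (64, 100, 95 %) and the output (50 to 78 %) stand in the same sentence, so the interval can be checked directly. It looks too wide: a proportion near 64 % in 100 people has a standard error of about 5 points, hence a 95 % half-width of about 9, not 14.

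Two things depend on the figure. First, it is the only numerical support offered for 64 participants. Secondly, its lower limit of 50 % is the same number as the success threshold. A reader who puts the example beside the rule will conclude that 64 of 100 only just passes and that a larger number of eligible people would fail. If the interval is wrong, so is that implied pass point. Anyone who reuses the printed precision to plan the later large trial would carry the error forward.

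**Working it through.** **Inputs.** Numerator 64, denominator 100, level 95 % and stated limits 50 and 78 % (Sample size). Binomial distribution and a lower-limit rule at 50 % (Statistical analyses; Abstract). 64 fixed and *N* observed (Table 2). The article names no interval method, so several were tried.

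**Step 1: try to reproduce 50 to 78 %.** With p = 0.64 and n = 100, the standard error is √(0.64 × 0.36 / 100) = 0.048.

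- Wald: 0.64 ± 1.96 × 0.048 = 0.64 ± 0.094, i.e. 54.6 to 73.4 %.
- Wilson: centre (0.64 + 3.8416/200) / (1 + 3.8416/100) = 0.6592/1.0384 = 0.6348. Half-width 1.96 × √(0.002304 + 3.8416/40000) / 1.0384 = 0.0925. Result 54.2 to 72.7 %.

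| Method, 95 %, 64/100 | Lower % | Upper % |
|---|---|---|
| Stated in the article | 50 | 78 |
| Wald | 54.6 | 73.4 |
| Wald, continuity-corrected | 54.1 | 73.9 |
| Wilson | 54.2 | 72.7 |
| Agresti-Coull | 54.2 | 72.7 |
| Jeffreys | 54.3 | 72.9 |
| Clopper-Pearson (exact) | 53.8 | 73.4 |
| Negative binomial (64 fixed, *N* observed) | 53.8 | 73.1 |

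The stated figure is not reproduced. Treating the count of 64 as Poisson does not match either (48.3 to 79.7 by normal approximation; 49.3 to 81.7 exact).

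**Step 2: how far off it is.** The stated half-width is 14 points. At n = 100 this needs z = 0.14/0.048 = 2.92, which is a 99.65 % Wald interval. Even the exact 99 % interval, 50.7 to 75.9 %, is narrower than the one labelled 95 %. Alternatively, keeping 95 %, the denominator would have to be 1.96² × 0.64 × 0.36 / 0.14² ≈ 45. Rounding or choice of method cannot close a gap of that size.

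**Step 3: the pass point with 64 randomised.** Find the largest *N* for which the lower 95 % limit of 64/*N* is at least 50 %.

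| *N* | 64/*N* % | Wald lower % | Wilson lower % | Exact lower % |
|---|---|---|---|---|
| 100 | 64.0 | 54.6 | 54.2 | 53.8 |
| 106 | 60.4 | 51.1 | 50.9 | 50.4 |
| 107 | 59.8 | 50.5 | 50.3 | 49.9 |
| 108 | 59.3 | 49.99 | 49.8 | 49.4 |

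Check for Wald at 107: p = 64/107 = 0.5981; 0.5981 − 1.96 × √(0.5981 × 0.4019 / 107) = 0.5981 − 0.0929 = 0.5052.

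The upper-tail probabilities agree with the exact limits. If half of eligible people can be randomised, P(X ≥ 64) is 0.0033 at *N* = 100, 0.0204 at 106 and 0.0263 at 107, against 0.025 for the lower side of a two-sided 95 % interval. The boundary is therefore 106 (exact) or 107 (Wald, Wilson, Agresti-Coull, Jeffreys). The criterion is worded as at least 50 % in the Abstract and over 50 % in Statistical analyses. That difference does not matter here, since no lower limit in the table equals 50 %.

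**The case against.** The strongest reply is that this is one illustrative sentence and that nothing in the trial turns on it. Much of that stands.

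- A reader might infer that the article sets 100 eligible people as a ceiling. It does not. The example is conditional and gives no maximum. The sentence after it speaks of a proportion of 50 % or more, not of a lower limit. The boundary at 100 appears only when the example is read together with the rule stated elsewhere.
- A reader might infer that the trial has less precision than planned. The reverse is true: the correct interval is narrower and its lower limit is higher.
- A reader might infer that the final feasibility verdict would be wrong. The Abstract, Statistical analyses and Table 2 all work from the observed *N*, so a correct analysis does not inherit the error.
- The probability of passing is not part of the point. It is about 81 % with a cut-off of 106 and 84 % with 107, but only if the true proportion is 64 %. The article uses 64 % as an example; its hypothesis is at least half.
- The denominator of about 45 in the working only measures the size of the discrepancy. Nothing in the article mentions 45 people, so it should not be taken as the source of the error.

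What the reply does not do is make the interval right. No other part of the article corrects it. A fuller protocol or analysis plan could not rescue it either, because inputs and result stand in the same sentence.

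**Conclusion.** The stated 95 % interval is wrong. For 64 of 100 it should be about 54 to 73 % (exact 53.8 to 73.4 %): the lower limit is about 4 points higher and the upper about 5 points lower than printed, and the width is about 19 points instead of 28. The pass point that the example implies for 64 randomised moves from 100 eligible people (64 %) to 106 by the exact method or 107 by Wald or Wilson (about 60 %).

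This rests on a two-sided 95 % binomial interval, as the article specifies, and on reading the example against the 50 % lower-limit rule. The choice between 106 and 107 depends on a method that the article does not name.

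The error is conservative and confined to the justification. It affects neither the sample size of 64 nor the decision rule. It should still be corrected, because it is the only precision figure behind the sample size and it coincides with the primary success threshold.

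**What to change.** Replace the example in the Sample size section with:

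> 64 of 100 gives 64 % (exact 95 % CI 54 to 73 %); with 64 randomised the exact lower limit is at least 50 % as long as no more than 106 eligible people are needed (60 %).

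Name the interval method there and use the same one in the final analysis. If Wald or Wilson is chosen, the figure is 107. Keep 64. If a different denominator was intended behind 50 to 78 %, state that denominator instead. The cost is one sentence, with no extra participants and no change to conduct or decision rule.
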